#### Routine care

The control group will receive routine care offered in the selected aged care centre (prescribed medications and routine activities). Routine care is the care offered to the participants according to the existing standard practices established in a particular care setting [40]. Routine care is often used for control groups, to compare a specific intervention (e.g., acupressure) with the existing practice in a selected setting [40]. In this study setting, the control group will be given daily routine care, nursing care, general healthcare, and specialised care based on the individual’s needs. The care given to control group will be equal to intervention group, except for the acupressure.

### Recruitment

The recruitment procedure will be carried out by the student researcher. The recruitment poster will be posted in the facility to advertise the research project, and flyers will be placed in reception and common areas of the facility. The student researcher will also promote the study during their routine social activities. She will present the study and then ask the potential participants for their expression of interest, either verbally or by contacting her via telephone or email. When the residents contact the student researcher and express interest in participating, the student researcher will explain the details of study procedures and provide them the participant information sheet and consent form. The researcher will assure that their participation in the study or decision to decline to participate will not affect the services they receive in the facility. If they agree to participate, information about inclusion and exclusion criteria will be identified on the basis of their medical records. Residents who give consent and meet the inclusion criteria will be enrolled in the study, given with a specific identification number (e.g., 001, 002). They will then be assigned to the intervention or control group, using random sequence numbers generated by the internet tool.

### Data collection

Data collection will be carried out by the researcher for pre-test, post-test, and 2-week post-test. The data collection timeline is shown in Table 2. The baseline data collection (pre-test, T0) will be conducted before commencing the acupressure intervention, using a structured questionnaire for demographic and clinical data and validated assessment tools for sleep quality, depression, anxiety and QoL. Demographic and clinical data include age, sex, marital status, number of children, education level, residential status, length of stay in facility, source of funding, presence of chronic disease, and medications.

**Table 2 Tab2:** Data collection timeline

Stages	Enrolment	Pre-test T0	4-Week acupressure intervention				Post-test, T1		Follow-up, T2
Time point	Week 0	Week 1	Week 2	Week 3	Week 4	Week 5	Week 6	Week 7	Week 8
Recruitment and consent	4–6 weeks								
Baseline assessment: - Demographic and clinical data - ActiGraph - PSQI, HADS, OPQOL-Brief		X							
Intervention: IG: acupressure + routine care CG: routine care			X	X	X	X			
Post-test outcome assessment: - ActiGraph - PSQI, HADS, OPQOL-Brief							X		
Follow-up assessment: - ActiGraph - PSQI, HADS, OPQOL-Brief									X

*CG* Control group, *HADS* Hospital Anxiety and Depression Scale, *IG* Intervention group, *OPQOL-Brief* Older People’s Quality of Life questionnaire–brief version, *PSQI* Pittsburgh Sleep Quality Index

The outcome assessments will be conducted at the end of intervention (post-test, T1) and 2 weeks post-intervention (post-test, T2). The participants will receive only routine care after the intervention period. The purpose of the follow-up test (T2) is to assess whether the treatment effect of acupressure can be retained 2 weeks after the intervention. For the control group, baseline and outcome data (T0, T1 and T2) will be collected using the same set of questionnaires and following the same time frame as in the intervention group. The student researcher will provide the assessment tools to the participants and assist them in completing the questionnaires if needed.

### Outcome assessments

The primary outcome for the acupressure intervention is sleep quality, which will be measured using the PSQI [41] and an objective sleep measurement device (ActiGraph, Pensacola, FL, USA). The secondary outcome measures include anxiety, depression and QoL. The Hospital Anxiety and Depression Scale (HADS) [42] will be used to measure anxiety and depression, and the brief Older People’s Quality of Life Questionnaire (OPQOL-Brief) [43] will be used to measure QoL.

#### Pittsburgh Sleep Quality Index

The PSQI measures a person’s subjective sleep quality over the previous 1-month time period. It consists of 19 items with seven sub-scores: subjective sleep quality, sleep latency, sleep duration, sleep efficiency, daytime dysfunction, sleep disturbances and use of sleeping medications [41]. The total score ranges from 0 to 21; higher scores indicates worse sleep quality, and a score greater than 5 indicates poor sleep quality [41].

The original version of the PSQI is a valid and reliable tool that is widely used to measure subjective sleep quality, with Cronbach’s α of 0.83 in healthy adults and individuals with sleep complaints and psychiatric symptoms [41]. The construct validity and internal consistency reliability in older adults was shown to be adequate, with the Cronbach’s α = 0.69 in older men [44] and α = 0.72 in older women [45].

In this study, sleep quality will be assessed before, immediately after and again 2 weeks after the intervention. To be consistent with the period between ratings, the time frame of the PSQI is modified as ‘during past two weeks’ instead of ‘during past month’. The modified version of the PSQI assesses sleep quality within the past 2 weeks.

#### Objective sleep measurement (ActiGraph)

The actigraphy device (ActiGraph GT9X Link) is equipped with a sensor that measures objective sleep patterns of a person. The ActiGraph is found to be a valid tool to determine the changes in sleep quality induced by specific intervention; therefore, it is suggested as a useful device for intervention studies [46]. To obtain reliable sleep data, the participants need to wear the device for a 1-week period [46, 47]. Therefore, the ActiGraph data will be recorded for 7 days before the intervention (T0), after the intervention (T1), and for 2 weeks post-intervention (T3). Participants will be asked to wear the device on the dominant wrist for 7 days and nights continuously, with it to be taken off only when showering. The data recorded by the ActiGraph will be downloaded and analysed using the ActiGraph software (ActiLife 6).

#### Hospital Anxiety and Depression Scale

The HADS is a tool for detecting emotional states of depression and anxiety in an adult population, and it is recommended for use in examining changes over time through intervention trial [42, 48]. It includes 14 items: seven items for anxiety and seven for depression. The HADS uses a 4-point Likert scale (0–3) for each item. The total score of anxiety and depression subscales ranges from 0 to 21; a higher score indicates higher level of depression or anxiety [42]. The HADS has shown good psychometric properties with good internal consistency in older adult samples: α = 0.84 for the anxiety subscale, and α = 0.75 for the depression subscale [48].

#### Brief Older People’s Quality of Life Questionnaire

The OPQOL-brief is a short version of the 35-item OPQOL questionnaire [43]. The total score ranges from 13 to 65; a higher score represents higher QoL. The OPQOL-brief was shown to be a reliable tool (α = 0.85), and it is a suitable tool for outcome assessment of social and health interventions in older people [43].

### Data analysis plan

Data will be analysed using IBM SPSS Statistics version 24.0 software (IBM, Armonk, NY, USA). The researcher will perform data entry using participants’ code numbers. The data will be explored and assessed for missing values, outliers, extreme values and normal distribution. Descriptive statistics will be used to explore baseline data. The generalised estimating equation (GEE) for repeated measurements will be used to examine the intervention effects on sleep quality, depression, anxiety and QoL. The primary outcome will be the treatment effect of acupressure on the post-treatment (T1) sleep quality scores measured by the PSQI and the ActiGraph. The post-treatment scores for the HADS and QoL will be used as secondary outcomes. The outcome data measured at 2-week follow-up will be analysed to determine the treatment effect of acupressure on the outcome variables (PSQI, ActiGraph, HADS and QoL scores) 2 weeks after the intervention.

Adjusted analyses will be conducted for age group; sex; use of sleep medication; and baseline PSQI, HADS and QoL scores. Sub-group analyses will be conducted to determine the differences in treatment effect of acupressure based on age group (65–85, 85–100, > 100 years) and use of sleep medication (yes/no). The correlation between outcome variables will be analysed (baseline, post-treatment, and 2-week follow-up), using Pearson or Spearman rank-correlation, depending on whether the data meet statistical assumptions. The statistical significance will be *P* < 0.05. The intention-to-treat method will be used that analyses participants according to their treatment allocation, regardless of deviation from the intervention protocol [49]. Missing-at-random assumption will be used to handle missing data in GEE analysis. The study flow diagram is shown in Fig. 2.

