### Sample size estimation

The sample size estimation is based on a previous study that indicated statistical significance in sleep quality between intervention and control group [23]. The mean difference of sleep quality (Pittsburgh Sleep Quality Index [PSQI] score) between groups was 5, and the pooled standard deviation was 6.35. To detect a mean difference of 5 points (assuming a standard deviation of 6.35), 26 participants in each group are required for a power of 0.80 and *P =* 0.05. Considering a 10% attrition rate, 29 participants in each group, with a total of 58 participants, are required.

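### The article makes PSQI and ActiGraph both primary at T1 under one unadjusted 5% level, but sizes the trial on the PSQI alone and gives no rule for a split result

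*Protocol article*

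**What the plan says.** Two sections of the protocol article give both instruments primary status. Outcome assessments says: "The primary outcome for the acupressure intervention is sleep quality, which will be measured using the PSQI [41] and an objective sleep measurement device". The Data analysis plan fixes the time point and repeats the pair: "The primary outcome will be the treatment effect of acupressure on the post-treatment (T1) sleep quality scores measured by the PSQI and the ActiGraph". The same section sets one threshold for everything: "The statistical significance will be *P* < 0.05". It describes no split of alpha, testing order or success rule.

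Sample size estimation uses one instrument. Its inputs are "The mean difference of sleep quality (Pittsburgh Sleep Quality Index [PSQI] score) between groups was 5" and "the pooled standard deviation was 6.35", and its result is "26 participants in each group are required for a power of 0.80". Allowing for 10% attrition, it arrives at 29 per arm and 58 in total. The article gives no ActiGraph effect or standard deviation anywhere.

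The Hypotheses section contains a single sleep hypothesis, significant improvement of sleep quality relative to control, and does not say which instrument decides it.

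**The concern.** The declared primary outcome has two measures, while the sample size has one. The error rate and power that a reader takes from the article (5% and 80%) belong to a single PSQI test. Whether they also belong to the trial depends on how the two results are combined, and the article does not say.

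A split result is plausible here. According to Randomisation and Limitations of the study, one unblinded researcher delivers the acupressure, collects the data and analyses them, with no sham or attention control. A self-reported score is more exposed to that than a wrist-worn device. If the PSQI were positive and the ActiGraph null, or the reverse, the published plan would not settle whether the sleep hypothesis had been supported.

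**Working it through.** **Inputs from the article.** PSQI difference 5; SD 6.35; power 0.80; significance level 0.05; 1:1 allocation; attrition 10%. Sidedness is not stated. Two-sided is assumed, because a one-sided calculation gives 20 per arm and does not fit the stated 26.

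**Inputs not in the article, so assumed.** The correlation between the two test statistics (range 0 to 0.9), and the power of the ActiGraph test (taken as 80%, equal to the PSQI).

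**Step 1: reproduce the stated sample size.** Per arm, n = 2 × [SD × (z for 0.975 + z for 0.80) / difference]² = 2 × [6.35 × (1.960 + 0.842) / 5]² = 25.3, rounded up to 26. With attrition, 26 / 0.90 = 28.9, so 29 per arm and 58 in total. The arithmetic is right for the PSQI tested alone at 0.05. At 26 per arm the power is 81.0% by the normal formula and 79.5% by the noncentral t.

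**Step 2: either measure suffices, each at 0.05.** For independent tests the false-positive rate is 1 − 0.95² = 9.75%. For correlated tests it is 1 − P(|Z1| < 1.96 and |Z2| < 1.96) under a bivariate normal distribution.

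| Correlation | False-positive rate |
|---|---|
| 0 | 9.75% |
| 0.3 | 9.5% |
| 0.5 | 9.1% |
| 0.9 | 7.0% |

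The rate is above 5% at any correlation below 1, and it rises further if more than one ActiGraph variable is counted.

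**Step 3: both measures required, each at 0.05.** Type I error is not inflated. With 80% power on each measure, joint power under independence is 0.80 × 0.80 = 64.0%. Otherwise it is the bivariate normal probability that both statistics exceed their critical values.

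| Correlation | Joint power |
|---|---|
| 0 | 64.0% |
| 0.3 | 66.6% |
| 0.5 | 68.7% |
| 0.9 | 75.0% |

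**Step 4: PSQI alone, or PSQI first and ActiGraph only if the PSQI is significant.** The first test uses the full 0.05 and the second is reached only through it. The 5% error rate holds, and so do 26 per arm before attrition and 29 after.

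**Step 5: what the other two rules would need for 80% power.** These figures assume that the ActiGraph has the same standardised effect as the PSQI, 5 / 6.35 = 0.787.
- Either measure, at 0.025 each, with 80% power per measure: 31 per arm, or 35 after attrition (70 in total). At the planned 26 per arm, power per measure falls to 72.5% (normal) or 70.1% (t).
- Both measures at 0.05, independent (the least favourable case): each needs power √0.80 = 89.4%, giving 34 per arm, or 38 after attrition (76 in total).

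All power figures follow the article's own comparison of two means. The planned GEE analysis with baseline adjustment could have different power.

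**The case against.** The strongest reply is that this is a condensed article. The full protocol exists in several versions, and a statistical analysis plan may exist too; neither is shown. An ActiGraph summary variable, a testing order and the handling of multiplicity are commonly fixed there. This stands: the unnamed ActiGraph variable and the absent success rule are not findings in themselves. What remains is a mismatch between things the article does state: two primary measures, one unadjusted level and a sample size for one measure.

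Some stronger readings are tempting, but the documents do not support them.

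- A reader might infer that the trial must have either inflated error or overstated power. That does not follow. A PSQI-first reading avoids both and fits the sample size section. The article does not state it, however, and its outcome and analysis sections give the two measures equal rank.
- A reader might infer that the 5% error rate is definitely breached. Inflation arises only under an either-measure rule, and the article's wording, which joins the measures with a conjunction, equally permits a rule requiring both. That each measure is tested at 0.05 is itself inferred from one general sentence.
- A reader might infer that the ActiGraph comparison is underpowered. Its power is unknown, not shown to be low.
- A reader might extend Step 2 to many ActiGraph variables and quote error rates near 20%, or combine an assumed low ActiGraph power with independence to reach joint power near 40%. The article supplies neither the number of variables nor the power that these figures need.

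It can also be said that making the PSQI the sole primary outcome demotes the only objective measure, although the Discussion presents the use of both as a strength. That is a fair cost, and a co-primary rule or a split alpha would be legitimate. Each would, however, need a larger sample than the one stated, under the equal-effect assumption of Step 5.

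**Conclusion.** The point holds as a mismatch within the article. The stated 5% and 80% are both true only of the PSQI as sole or first-tested primary outcome, and the article does not say that it is. Under an either-measure rule the false-positive rate is about 9-10% for two tests at correlations of 0 to 0.5, and 7.0% at 0.9. Under a both-measures rule the error rate is sound, but joint power is about 64-75% rather than 80%, given an assumed 80% power for the ActiGraph and correlations of 0 to 0.9. The correlation and the ActiGraph power are assumptions, so these are ranges and not estimates for this trial. That neither rule delivers the stated pair of figures does not depend on the correlation chosen, short of perfect correlation. It matters because it determines what counts as a positive result.

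**What to change.** Name the PSQI total score at T1 as the sole primary outcome, which matches the sample size and leaves 26 per arm (29 with attrition) unchanged. Name one ActiGraph variable as the first key secondary outcome, tested at 0.05 only if the PSQI is significant. Report the other ActiGraph variables as secondary, with confidence intervals. State that an ActiGraph result alone cannot make the trial positive.

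No extra participants are needed. The cost is that the primary claim then rests on self-report in an unblinded trial, so the ActiGraph result should always be reported beside the PSQI result, whatever it shows.

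This is no longer only a prospective change of wording, because Trial status records that the project was completed on 15 April 2020. The report should say whether this order was fixed, in the full protocol or an analysis plan, before outcome data were seen. If it was not, the order should be labelled post hoc.

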### Setting and participants

This study will be conducted in three RACFs (RACFs 1, 2 and 3) in New South Wales State, Australia. The selected study venues are facilities accredited by the Aged Care Quality and Safety Commission, Australia. These facilities offer general healthcare for the residents and specialised aged care services, such as dementia care and palliative care. Study participants will be older people residing in the study venues.

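### The adjusted-analysis covariate list omits baseline ActiGraph, although ActiGraph sleep at T1 is a primary measure and its T0 value is already recorded

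*Protocol article*

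**What the plan says.** All of this is in the protocol article. The Data analysis plan defines the primary outcome: "The primary outcome will be the treatment effect of acupressure on the post-treatment (T1) sleep quality scores measured by the PSQI and the ActiGraph". The model is a repeated-measures GEE: "The generalised estimating equation (GEE) for repeated measurements will be used to examine the intervention effects on sleep quality, depression, anxiety and QoL". The next paragraph gives the covariates: "Adjusted analyses will be conducted for age group; sex; use of sleep medication; and baseline PSQI, HADS and QoL scores". Sub-group analyses follow in the same paragraph.

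The baseline ActiGraph value exists. The section on objective sleep measurement says "the ActiGraph data will be recorded for 7 days before the intervention (T0", and Table 2 under Data collection lists the ActiGraph at baseline next to PSQI, HADS and OPQOL-Brief.

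The plan does not say which GEE, with or without covariates, decides the primary comparison. Nor does it say whether the T0 value is one of the repeated outcomes or a covariate.

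**The concern.** The covariate list is explicit and looks complete: it contains the baseline of PSQI, HADS and QoL. The only outcome instrument left out is one of the two that carry the primary outcome. A measure's own baseline is usually its strongest available predictor, whereas baseline anxiety, depression and QoL are likely to be weaker predictors of an actigraphy variable. The plan therefore adjusts ActiGraph for the less useful covariates and leaves out the most useful one.

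Two things are at stake. The first is precision in a trial planned on 26 evaluable participants per group. The second is a fixed choice of analysis: if a GEE is run both with and without covariates and neither is named in advance, a reader cannot tell which result answers the primary question. That matters more here because, by the article's own account (Randomisation; Limitations of the study), the unblinded researcher who gives the acupressure also collects and analyses the data.

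**Working it through.** **1. The plan's own figure.** Inputs from Sample size estimation: "The mean difference of sleep quality (Pittsburgh Sleep Quality Index [PSQI] score) between groups was 5, and the pooled standard deviation was 6.35"; "26 participants in each group are required for a power of 0.80 and" a significance level of 0.05. Sidedness is not stated; two-sided reproduces the figure, while one-sided gives 20.

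n per group = 2 × [6.35 × (1.960 + 0.842) / 5]² = 25.3, rounded up to 26 (a t-based calculation gives 26.3). With 10% attrition, 26 / 0.90 = 28.9, so 29 per group and 58 in total. The figure reproduces. It rests on a plain comparison of two means with no baseline correlation.

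Power at 26 per group: SE = 6.35 × √(2/26) = 1.76, and power = Φ(5/1.76 − 1.96) = 0.81 (t-based: 0.795).

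**2. Own-baseline adjustment.** Let r be the correlation between T0 and T1 of the same measure. The documents give no value, so r is an assumption. With equal variances at T0 and T1, the variance of the treatment contrast relative to an unadjusted T1 comparison is:

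- unadjusted T1 comparison: 1
- change contrast (T0 as an outcome, free group-by-time term): 2(1 − r)
- own baseline as covariate: 1 − r²
- own baseline relative to change contrast: (1 − r²) / [2(1 − r)] = (1 + r)/2

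Power below is for PSQI with 26 per group, difference 5, and SD 6.35 multiplied by the square root of the factor.

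| Assumed r | 1 − r² | Fall vs unadjusted T1 | Power, own baseline | n per group for 80% | Power, change contrast | (1 + r)/2 | Fall vs change contrast |
|---|---|---|---|---|---|---|---|
| 0.3 | 0.91 | 9% | 0.85 | 24 | 0.67 | 0.65 | 35% |
| 0.5 | 0.75 | 25% | 0.91 | 19 | 0.81 | 0.75 | 25% |
| 0.7 | 0.51 | 49% | 0.98 | 13 | 0.96 | 0.85 | 15% |

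Example at r = 0.5: SD = 6.35 × √0.75 = 5.50; SE = 5.50 × √(2/26) = 1.53; power = Φ(5/1.53 − 1.96) = 0.91.

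**3. ActiGraph.** No ActiGraph SD or effect size is given, so only variance ratios apply. As an illustration, if baseline PSQI correlates 0.1 to 0.3 with T1 ActiGraph (an assumption), adjusting for it alone removes 0.1² to 0.3², or 1% to 9%, of variance. ActiGraph's own baseline at r = 0.5 to 0.7 removes 25% to 49%.

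**4. Why the role of T0 matters.** Suppose T0, T1 and T2 are all outcomes, with a free group-by-time term and complete data. The group-by-T1 coefficient is then the difference between groups in mean change, and a time-fixed covariate added as a main effect cancels from it. A simulated check (N = 52, r = 0.5) agrees: −0.206, SE 0.245, with and without baseline and sex. With about 10% dropout the equality is only approximate: a second simulation (N = 58, exchangeable working correlation) gave −0.456 (SE 0.264) without baseline and −0.462 (SE 0.265) with it. With only T1 and T2 as outcomes, own-baseline adjustment did work: in the first simulation the SE fell from 0.234 to 0.194.

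A third set-up keeps T0 as an outcome but constrains the baseline means to be equal. With a working correlation that links T0 to T1, baseline is then already used almost fully and the further gain is close to nil.

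**The case against.** The strongest reply is that the article does not say how T0 enters the GEE. If T0 is one of the repeated outcomes, baseline ActiGraph is already in the model, and leaving it off the covariate list costs little or nothing. The loss of r² arises only if T1 and T2 alone are outcomes and the model is unadjusted, which is not stated either. This stands: the size of the gain is conditional. It does not rescue the list, because in that set-up, with complete data, the listed baseline PSQI would do nothing for the PSQI comparison either.

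A second reply is that the choice of decisive model and the handling of T0 are commonly left to an analysis plan or full protocol, neither of which is at hand. That also stands, so their absence is not an error in itself. The ActiGraph omission is different: the article chose to give the list, and the list leaves out one primary measure.

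Third, a reader might infer that the main GEE is unadjusted and that adjustment is only an extra. The Discussion, which mentions adjusted and sub-group analyses together, encourages this. But the text never calls the main GEE unadjusted, and the covariate sentence could equally describe the covariates of that GEE. All that can be said is that the matter is open.

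**Conclusion.** The omission is real and stands on the text: ActiGraph sleep at T1 is primary, its baseline is recorded, and the explicit covariate list leaves it out. Correcting it is a free improvement. It brings precision and removes a choice between two analyses.

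Under assumed r of 0.3, 0.5 and 0.7, the variance reduction is 9%, 25% and 49% against an unadjusted T1 comparison, and 35%, 25% and 15% against a change contrast. It is close to nil if baseline means are already constrained equal. For PSQI the first case takes power from 0.81 to 0.85, 0.91 and 0.98; no power can be computed for ActiGraph.

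Stronger readings are not supported. A reader might infer that the primary comparison is biased or the trial underpowered. The unadjusted randomised comparison is unbiased, and 26 per group gives about 80% power for PSQI on the plan's own inputs without any adjustment. A reader might also think the planned adjustment is always inert; that needs T0 in the outcome vector, a free group-by-time term and complete data together. Adding facility, using continuous age, or dropping baseline HADS and QoL are matters of preference; the documents show no defect that requires them.

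**What to change.** For each primary measure, name one primary GEE:

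- outcomes at T1 and T2 only, with treatment by visit, and the T1 contrast as the primary comparison;
- that measure's own T0 value as a continuous covariate: baseline PSQI for PSQI, and the same 7-night variable at T0 for each ActiGraph model;
- T0 stated to be a covariate and not also an outcome;
- the unadjusted GEE reported as a sensitivity analysis.

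In the covariate sentence, add baseline ActiGraph for the ActiGraph models. The cost is wording and one regression coefficient per model. No new data, visits or participants are needed, and 26, 29 and 58 can stay as they are.
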